## Abstract

**Background:**

Ayurveda recommends a comprehensive therapeutic approach for osteoarthritis management. However, most of the published clinical studies on Ayurveda interventions for osteoarthritis management have addressed selected modalities of Ayurveda treatment rather than the holistic therapeutic regimen.

**Objective:**

This study aimed to assess the efficacy and safety of a multimodal Ayurveda treatment protocol in the long-term management of primary osteoarthritis of the knee compared with standard care.

**Methods:**

The proposed open-label, parallel-group randomized controlled trial was conducted in individuals of any gender aged 40 to 70 years and diagnosed with primary osteoarthritis of the knee as per the American College of Rheumatology criteria. Individuals with grade 4 radiographic changes in the affected knee (based on the Kellgren-Lawrence classification) and with comorbidities were not considered. The study was conducted at the All India Institute of Medical Sciences, New Delhi, India. A total of 150 participants underwent random assignment in a 1:1 ratio to receive either the Ayurveda treatment protocol or conventional standard care for 180 days. The primary outcome was the change in the Western Ontario and McMaster Universities Osteoarthritis Index score from baseline. The secondary outcome measures included the change in the score for pain, stiffness, and physical function from baseline; change in the range of motion of the knee joint; change in the score of the numeric pain rating scale, Pain Disability Index, and 12-item short-form survey questionnaire (to assess health-related quality of life); change in highly sensitive C-reactive protein levels, interleukin-6 levels, magnetic resonance imaging scan findings, and dual-energy X-ray absorptiometry scan findings; and change in the need for rescue analgesic medication from baseline. Safety was evaluated by recording the incidence of adverse events and changes in liver and kidney function tests from baseline.

**Results:**

Recruitment of study participants commenced on October 11, 2022. Currently, all the participants completed the study and the analysis of the study outcomes is ongoing.

**Conclusions:**

This randomized controlled trial will be the first study to explore the potential benefits of a multimodal Ayurveda regimen (based on Ayurveda principles and scientific evidence) in the long-term management of osteoarthritis of the knee through validated subjective, laboratory, and imaging parameters. The outcomes of this study may address the needs and challenges associated with osteoarthritis management.

**Trial Registration:**

Clinical Trial Registry of India CTRI/2022/05/042792; 
https://ctri.nic.in/Clinicaltrials/pmaindet2.php?EncHid=Njk0MTM=&Enc=&userName=

**International Registered Report Identifier (IRRID):**

DERR1-10.2196/68306

## Introduction

### Background

Osteoarthritis is a chronic degenerative condition characterized by structural changes in the articular cartilage, ligaments, capsule, synovium, subchondral bone, and periarticular muscles, resulting in joint pain, stiffness, and limited mobility [1]. As per the Osteoarthritis Research Society International, osteoarthritis has all the hallmarks of a serious condition because of associated disability and loss of function [2]. Osteoarthritis most commonly affects the knee, followed by the hand, hip, spine, and shoulder. Osteoarthritis of the knee accounts for approximately 85% of osteoarthritis cases globally [3]. Primary osteoarthritis is caused by age-related degeneration, while secondary osteoarthritis occurs because of injury, occupation-related stress on joints, and comorbid conditions, including diabetes mellitus. Mechanical, inflammatory, and metabolic factors play an important part in the intricate pathophysiology of osteoarthritis, which eventually results in the structural breakdown and collapse of the synovial joint [4]. Global estimates indicate that approximately 595 million individuals worldwide were affected by this burdensome clinical condition in 2020, equivalent to 7.6% of the global population [5]. Osteoarthritis is becoming more prevalent owing to the combined impacts of aging, rising physical inactivity and obesity in the population, and an increased incidence of joint injuries [2]. In 2020, 21.7 million years lived with disability were attributed to osteoarthritis globally [5]. It is one of the 4 leading causes of years lived with disability worldwide [4]. The objectives of osteoarthritis management are to reduce pain intensity and inflammation, slow down cartilage degradation, improve joint movement, and reduce disability. Treatment options include patient education, oral and topical pharmacological agents, interventional procedures (eg, corticosteroid injection and viscosupplementation), bracing, assistive devices, physical therapy, and surgery (eg, arthroscopy, osteotomy, and arthroplasty) [6]. Currently, conventional medicine has no therapeutic options that can arrest or slow down the disease progression in patients with osteoarthritis [2]. In the absence of drugs with proven disease-modifying activity, the current approach is mainly focused on palliative pain management [7]. However, chronic pain management with acetaminophen, nonsteroidal anti-inflammatory drugs, and intermittent intra-articular corticosteroid injections is associated with limited benefits, along with considerable gastrointestinal, renal, and cardiovascular risks [2,8-10]. Furthermore, there is uncertainty regarding the effect of glucosamine and chondroitin supplementation on the structural progression of osteoarthritis [10]. Meanwhile, arthroplasty is considered only for severe cases of osteoarthritis. Therefore, it is pertinent to search for safe, efficacious, and cost-effective therapeutic options with better tolerability to reduce the disease burden of osteoarthritis.

*Sandhigatavata*, a specific type of *Vatavyadhi* (disease conditions because of vitiation of *Vata Dosha*) in Ayurveda, has a clinical presentation similar to osteoarthritis. Ayurveda suggests a multimodal treatment approach for managing *Sandhigatavata*, a traditional Ayurvedic condition clinically comparable to osteoarthritis, including a judicious combination of *Panchkarma* (Ayurveda therapeutic procedures), oral medications, nutritional supplements, a nutritious diet, and a recommended lifestyle. Several published clinical studies have highlighted the safety and beneficial effects of Ayurveda interventions in the management of osteoarthritis [11-23]. One randomized controlled trial (RCT) concluded that the Ayurveda treatment protocol led to significant and clinically relevant improvement in osteoarthritis-related clinical features compared with conventional care, with most effects maintained over 12 months [11,12]. Another clinical study, supported by the World Health Organization to evaluate the feasibility of operational integration of Ayurveda treatment with conventional medicine in the management of osteoarthritis of the knee at a tertiary care hospital, also reported that the Ayurveda treatment regimen showed promising outcomes in the management of osteoarthritis of the knee, including symptom reduction, improved quality of life, and reduced need for conventional analgesics [13]. A systematic review also highlighted the safety and preliminary evidence regarding the effectiveness of various Ayurveda interventions in the management of osteoarthritis [24]. In addition, Ayurveda interventions, such as *Shallaki* (*Boswellia serrata* Roxb.)*, Guggulu* (*Commiphora mukul* Engl.)*, Ashwagandha* (*Withania somnifera* [L.] Dunal)*, Shunthi* (*Zingiber officinale* Roscoe)*, Bala* (*Sida cordifolia* L.)*, Nirgundi* (*Vitex negundo* L.)*,* and *Dashmula* (a combination of the dried root of 10 specific medicinal plants) have shown potential anti-inflammatory, analgesic, antiosteoporotic, and antioxidant activities [25-33].

However, most of the aforementioned published studies have addressed selected modalities of Ayurveda treatment rather than a holistic Ayurveda therapeutic regimen. Therefore, it is necessary to conduct RCTs with a multimodal Ayurveda regimen for the management of osteoarthritis. Considering this limitation, the present RCT was conceptualized to assess the efficacy and safety of an Ayurveda treatment regimen (consisting of therapeutic procedures and oral medications) to manage primary osteoarthritis of the knee. The therapeutic regimen proposed for the study is based on preliminary leads from exploratory clinical studies on individual Ayurveda interventions that have shown promising outcomes in the management of osteoarthritis [15,17,18].

### Objectives

The present RCT was designed to assess the efficacy of multimodal Ayurveda interventions in managing pain and functional disability in patients with primary osteoarthritis of the knee compared with standard care. The key secondary objectives of this study included evaluating the efficacy of the trial Ayurveda interventions on range of motion of the knee joint, the need for rescue analgesic medication, quality of life parameters, knee structural changes (ie, delay in the structural progression of osteoarthritis), proinflammatory biomarkers, and bone mineral density after 180 days. Another secondary objective was to assess the safety of multimodal Ayurveda interventions in managing osteoarthritis of the knee.

## Methods

The study protocol has been drafted following the SPIRIT (Standard Protocol Items: Recommendations for Interventional Trials) guidelines [34].

### Study Design and Setting

This clinical study was an open-label, randomized, controlled, parallel-group, noninferiority trial. The study was conducted at the All India Institute of Medical Sciences (AIIMS), New Delhi, India.

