### Outcome Measures

The primary outcome was the change in the Western Ontario and McMaster Universities Osteoarthritis Index (WOMAC) score from baseline. The secondary outcome measures included the change in the score for pain, stiffness, and physical function from baseline (assessed using the WOMAC scale); the change in range of motion of the knee joint (assessed using a goniometer); the change in the scores of the numeric pain rating scale, Pain Disability Index, and 12-item short-form survey questionnaire (to assess health-related quality of life); the change in high-sensitivity C-reactive protein and interleukin-6 levels, MRI findings (to assess knee structural changes), and dual-energy x-ray absorptiometry scan findings (to assess change in bone mineral density); and the change in the need for rescue analgesic medication.

The outcomes were evaluated every 30 days until day 180 from baseline. Laboratory investigations were conducted at baseline and on day 180.

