### Sample Size

On the basis of the results from a previous study [11], in which the difference in WOMAC score between the Ayurveda and conventional group after 12 weeks of treatment was 24 points, this study has been designed to have 80% statistical power to detect a difference of at least a 20-point improvement (change from baseline) in the WOMAC score after treatment between the 2 groups (pooled SD 42; 2-sided *t* test, α=.05). To achieve this, 69 participants per group were required. Accounting for an expected attrition rate of 10%, the final sample size for each group was determined to be 75 participants (150 in total).

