### Statistical Methods

Categorical data will be presented as numbers (percentages) and compared between groups using the chi-square test. Continuous data following normal distributions will be reported as mean (SD), and between-group comparisons will be performed using the independent sample *t* test. Within-group comparisons for normally distributed data will be conducted using the paired sample *t* test or repeated measures ANOVA. Nonnormally distributed data will be reported as median (first and third quartiles), and between-group comparisons will be performed using the Mann-Whitney *U* test. Within-group comparisons will be conducted using the Wilcoxon signed rank test or the Friedman test. A *P* value <.05 will be considered statistically significant. SPSS software (version 29.0; IBM Corp) will be used for statistical analysis.

The modified intention-to-treat analysis approach will be applied to handle missing data. Missing data for all participants with available data from at least 1 visit after baseline (day 30) will be imputed. The last observation carried forward method will be used to impute the missing values.

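### The article labels the trial noninferiority, but its sample size and tests describe a superiority comparison and it states no margin

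*Protocol article*

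**What the plan says.** The protocol article describes its design in several places.

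- **Study Design and Setting:** "This clinical study was an open-label, randomized, controlled, parallel-group, noninferiority trial". The word noninferiority appears nowhere else in the article.
- **Abstract, Methods:** "The proposed open-label, parallel-group randomized controlled trial was conducted in individuals of any gender aged 40 to 70 years", with no mention of noninferiority.
- **Objectives:** the trial is described as "designed to assess the efficacy of multimodal Ayurveda interventions in managing pain and functional disability in patients with primary osteoarthritis of the knee"; the comparator is standard care. This wording is neutral between the two frameworks.
- **Outcome Measures:** "The primary outcome was the change in the Western Ontario and McMaster Universities Osteoarthritis Index (WOMAC) score from baseline".
- **Sample Size:** the trial has "80% statistical power to detect a difference of at least a 20-point improvement (change from baseline) in the WOMAC score" between the groups, with pooled SD 42 and a 2-sided t test at .05. The planning value comes from a previous study in which "the difference in WOMAC score between the Ayurveda and conventional group after 12 weeks of treatment was 24 points". The result is 69 per group, raised to 75 for 10% attrition (150 in total).
- **Statistical Methods:** groups are compared by an independent-sample t test or a Mann-Whitney U test, and a P "value <.05 will be considered statistically significant".

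**The concern.** A noninferiority trial asks whether the new treatment is worse than the comparator by more than a stated amount, and answers by setting a confidence limit against that amount. A superiority trial asks whether the groups differ. The article claims the first design and specifies the second.

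The two frameworks agree when Ayurveda is significantly better, since that result supports both claims. They part when the result is nonsignificant. Under superiority, the trial has then not shown a difference. Under a noninferiority label with no margin, a reader has no stated rule for deciding whether the trial succeeded, and a nonsignificant P value can be mistaken for evidence that Ayurveda is no worse than standard care.

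Timing matters too. The Abstract reports that all participants have completed and that analysis is under way, so a margin chosen now would carry little weight.

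**Working it through.** **Inputs.** From Sample Size: difference 20, SD 42, 2-sided alpha .05, power 80%, 69 evaluable and 75 enrolled per group, 10% attrition. Margins are not given, so those used in step 4 are assumptions shown as a range.

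**1. Reproduce the stated 69.** For a 2-sided comparison of two means,

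n per group = 2 × [SD × (1.960 + 0.842) / difference]² = 2 × (42 × 2.8016 / 20)² = 69.2.

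Rounded up this is 70; the t-based calculation gives 70.2, or 71. The stated 69 is within two participants of both, and power at 69 is 79.9% (normal) or 79.3% (t). A one-sided .05 calculation gives 55, which does not match. For attrition, 69 / 0.90 = 76.7 against 75 stated, a small difference that does not affect this point. The 20 points therefore enter as a difference to be detected.

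**2. Precision.** With 69 evaluable per group, SE = 42 × √(2/69) = 7.15, and the 95% CI half-width is 1.96 × 7.15 = 14.0 points. If 10% of 75 are lost, 75 × 0.90 = 67.5 remain. With 67 and 68, SE = 42 × √(1/67 + 1/68) = 7.23, and the t-based half-width is 14.3 points.

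**3. What a nonsignificant P value would mean.** For a true deficit d of Ayurveda against control,

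P(nonsignificant) = Φ(1.96 − d/SE) − Φ(−1.96 − d/SE).

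| True deficit (WOMAC points) | 69 per group (normal) | 67 and 68 (noncentral t) |
|---|---|---|
| 0 | 95% | 95% |
| 5 | 89% | 89% |
| 10 | 71% | 72% |
| 15 | 45% | 46% |

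For d = 10 and 69 per group, d/SE = 1.40, and Φ(0.56) − Φ(−3.36) = 0.71. A true deficit of half the planned effect would usually give P>.05.

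**4. Noninferiority sample size under assumed margins.** With true difference 0, one-sided .025 and 80% power, n per group = 2 × (42 × 2.8016 / margin)².

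| Assumed margin (points) | Evaluable n per group | With 10% attrition | Power with 69 evaluable |
|---|---|---|---|
| 5 | 1108 | 1232 | 10% |
| 10 | 277 | 308 | 29% |
| 15 | 124 | 138 | 56% |
| 20 | 70 | 78 | 80% |

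The second column compares with 69 evaluable in the plan, and the third with 75 enrolled.

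**The case against.** The best defence is that the same 69 per group gives about 80% noninferiority power at a 20-point margin, because the algebra is identical, and that a 2-sided 5% t test yields a 95% confidence interval that can be read against a margin at one-sided 2.5%. Both statements are true: the planned test is usable for noninferiority once a margin and rule are fixed. They do not rescue the label. The article presents 20 points as an improvement to detect and never as a margin. As a margin it would tolerate a deficit as large as the benefit the trial was sized to find, and 20/24 (83%) of the difference cited from the previous study.

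Four stronger readings are tempting, and the documents support none of them.

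- **That no margin was ever set.** Only a condensed article is at hand. A full protocol or SAP may contain one; its absence is established for this article alone.
- **That the trial is too small for noninferiority by a known factor.** The requirement runs from 70 to 1108 per group as the assumed margin runs from 20 to 5 points, so no single shortfall can be quoted.
- **That the sponsor intends to report a nonsignificant result as noninferiority.** No section plans this. It is a risk left open by the wording.
- **That modified intention-to-treat with last observation carried forward would favour a noninferiority claim.** The direction of that bias depends on when participants drop out and how each arm is changing, which the article does not give.

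It is also fair to say that no formal hypothesis is written. Superiority is inferred from the sample-size wording, the 2-sided test and the P<.05 rule. And the conflict is one word in one section, whose correction under the superiority reading changes no planned analysis.

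**Conclusion.** The contradiction holds. The design label conflicts with the sample size and the tests, and no other section of the article reconciles them. An unseen document could supply a margin, but it could not make these sections agree as they stand, so a correction is needed either way.

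Its importance is that the label governs what the primary result can mean. Under the stated rule, a nonsignificant difference would leave an interval of about 14 points either side of the estimate and would be the usual result (71% to 72%) even if Ayurveda were truly 10 points worse. These figures rest on the article's SD of 42, 67 to 69 evaluable participants per group, and a comparison of means. The sample-size calculation itself is sound to within rounding as a superiority calculation.

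**What to change.** First establish whether a margin and decision rule are documented in a dated protocol version that predates study completion.

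- **If so,** cite that version and align Sample Size and Statistical Methods with it. Deleting the label in that case would itself be a change of design after completion.
- **If not,** remove the word noninferiority from Study Design and Setting. State a superiority hypothesis on the between-group difference in WOMAC change, tested 2-sided at 5%. Add that a nonsignificant difference will be reported with its 95% confidence interval and will not be interpreted as noninferiority or equivalence.

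Date the clarification before allocation is unblinded. The Limitations section says the analysing statistician will be blinded to allocation, so this may still be possible, but analysis is already in progress and the record should show what had been seen by then.

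Under the superiority route the cost is a wording change, with no new data and no change to the planned tests. What is given up is a noninferiority claim that the article's stated design does not support.

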### Study Participants

Individuals of any gender aged 40 to 70 years who were diagnosed with primary osteoarthritis of the knee as per the American College of Rheumatology (ACR) criteria; had a pain score of at least 2 (as per the numeric pain rating scale) on most days in the last month; met ACR functional status criteria class I, II, and III; have a serum vitamin D level >30 ng/mL; and were willing to provide written informed consent were included in the study. The ACR criteria for osteoarthritis of the knee include knee pain along with any 3 of the following: aged >50 years, joint stiffness lasting less than 30 minutes, crepitus, bony tenderness, bony enlargement, and absence of palpable warmth.

Individuals were excluded if they had grade 4 radiographic changes in the affected knee joint (as per the Kellgren-Lawrence classification); had a history of significant trauma to the knee (including arthroscopy within the preceding year), knee joint replacement, intra-articular corticosteroid or hyaluronic acid administration within 1 month before the study; were currently taking corticosteroids; or had a history of rheumatoid arthritis, psoriatic arthritis, systemic lupus erythematosus, cardiovascular disease, or malignancy. Individuals were also excluded if they had uncontrolled diabetes mellitus (ie, hemoglobin A_1c_ >8%), uncontrolled hypertension (ie, blood pressure >160/100 mm Hg despite medication), abnormal hepatic function (ie, aspartate aminotransferase or alanine aminotransferase >2 times the upper limit of normal), or abnormal renal function (ie, serum creatinine >1.2 mg/dL); a tendency for occurrence of recurrent renal calculi; or a BMI ≥32 kg/m^2^. Similarly, those with any contraindication for magnetic resonance imaging (MRI), a history of hypersensitivity to the study interventions, a history of chain smoking, alcohol use disorder, substance abuse, or any other clinical condition that the investigator believed may compromise the participant’s safety, compliance, or evaluation were not considered for the study.

### Study Intervention

Eligible participants in the Ayurveda group received a comprehensive Ayurveda treatment protocol, which included *Matra Basti* with *Ksheerabala Taila* and *Janu Basti* with *Dhanwantara Taila*, along with oral medications—*Laksha Guggulu* and *Muktashukti Bhasma*—for 180 days. The details of the study interventions are provided in Table 1.

**Table 1 table1:** Details of the study interventions.

Intervention (with reference)	Route of administration	Dosage and frequency	*Anupana* (vehicle of administration)	Duration
*Ksheerabala Taila* (API^a^ part II, vol I [35])	Rectal (*Matra Basti*)	60 mL once daily after food	—^b^	14 d every 2 mo for 180 d
*Dhanwantara Taila* (API part II, vol I [35])	Local application over the affected knee (*Janu Basti*)	QS^c^ once daily	—	14 d every 2 mo for 180 d
*Laksha Guggulu* (API part II, vol II [36])	Oral	1 g twice daily after food	Lukewarm water	180 d
*Muktashukti Bhasma* (Pharmacopeial Standards for Ayurvedic Formulations [37])	Oral	250 mg twice daily after food	Lukewarm water	180 d

^a^API: Ayurvedic Pharmacopoeia of India.

^b^Not applicable.

^c^QS: quantity sufficient.

The methodology of the therapeutic procedures, *Matra Basti* and *Janu Basti*, is provided in Multimedia Appendix 1. The participants in the control group will receive standard care (ie, topical application of diclofenac sodium gel twice daily) for 180 days, as recommended in the standard treatment guidelines for the management of osteoarthritis of the knee, issued by the Ministry of Health and Family Welfare, Government of India.

Ayurveda practitioners on the research team dispensed the Ayurveda interventions at the study sites throughout the trial period. Furthermore, paramedical staff trained in *Panchakarma* administered *Matra Basti* and *Janu Basti* to the study participants in the Ayurveda group. The participants were examined every 30 days during the study period. The trial Ayurveda interventions were procured from the Indian Medicines Pharmaceutical Corporation Limited, Ministry of Ayush, Government of India.

